## Abstract

**Background:**

Walking recovery post stroke can be slow and incomplete. Determining effective stroke rehabilitation frequency requires the assessment of neuroplasticity changes. Neurobiological signals from electroencephalogram (EEG) can measure neuroplasticity through incremental changes of these signals after rehabilitation. However, changes seen with a different frequency of rehabilitation require further investigation. It is hypothesized that the association between the incremental changes from EEG signals and the improved functional outcome measure scores are greater in higher rehabilitation frequency, implying enhanced neuroplasticity changes.

**Objective:**

The purpose of this study is to identify the changes in the neurobiological signals from EEG, to associate these with functional outcome measures scores, and to compare their associations in different therapy frequency for gait rehabilitation among subacute stroke individuals.

**Methods:**

A randomized, single-blinded, controlled study among patients with subacute stroke will be conducted with two groups: an intervention group (IG) and a control group (CG). Each participant in the IG and CG will receive therapy sessions three times a week (high frequency) and once a week (low frequency), respectively, for a total of 12 consecutive weeks. Each session will last for an hour with strengthening, balance, and gait training. The main variables to be assessed are the 6-Minute Walk Test (6MWT), Motor Assessment Scale (MAS), Berg Balance Scale (BBS), Modified Barthel Index (MBI), and quantitative EEG indices in the form of delta to alpha ratio (DAR) and delta-plus-theta to alpha-plus-beta ratio (DTABR). These will be measured at preintervention (R0) and postintervention (R1). Key analyses are to determine the changes in the 6MWT, MAS, BBS, MBI, DAR, and DTABR at R0 and R1 for the CG and IG. The changes in the DAR and DTABR will be analyzed for association with the changes in the 6MWT, MAS, BBS, and MBI to measure neuroplasticity changes for both the CG and IG.

**Results:**

We have recruited 18 participants so far. We expect to publish our results in early 2023.

**Conclusions:**

These associations are expected to be positive in both groups, with a higher correlation in the IG compared to the CG, reflecting enhanced neuroplasticity changes and objective evaluation on the dose-response relationship.

**International Registered Report Identifier (IRRID):**

DERR1-10.2196/27935

## Introduction

Stroke is one of the most common causes of death and acquired disability worldwide, affecting motor function, speech, swallowing, vision, sensation, and cognition, and poststroke recovery can be slow and incomplete [1,2]. Stroke has been reported by Malaysia’s Ministry of Health to be the third leading cause of mortality and morbidity [3]. The rehabilitation process should begin within the first few days after stroke to maximize neurological and functional recovery to achieve the highest possible level of independence. However, rehabilitation therapy for stroke is long term and time-consuming, and can be expensive with the use of advanced equipment or gadgets [4,5]. Hence, determining effective and tailored stroke rehabilitation therapy within limited resources is a matter of priority [6]. Rapid and accurate decision-making is critical to stroke rehabilitation care, for which several factors have proven to affect the stroke outcomes, including therapy frequency, intensity, and task-specific training [7].

Motor learning through stroke rehabilitation is proven to promote cortical reorganization and neuronal synaptogenesis that form the basis of the neuroplasticity concept [8]. Neuroplasticity is the ability for the brain to repair and reorganize after acquiring an injury such as stroke and is primarily affected by three main factors: therapy frequency, intensity, and task-specific training [9-11]. At present, choosing the best rehabilitation therapy for stroke patients is, in part, a trial-and-error process that can take weeks. However, recovery capacity after stroke declines overtime in which maximum recovery is demonstrated within the first 6 months after stroke [12]. It is imperative to choose an effective rehabilitation regime for promoting neuroplasticity within the recovery period. For the majority of clinical settings in lower-income regions, rehabilitation medicine experts assess and decide the best rehabilitation therapy for poststroke patients. Decisions are made based on subjective assessments that may result in contradicting patients’, families’, and relatives’ expectations, and potentially inappropriate advice, treatment, or discharge. Hence, an objective assessment is needed to demonstrate and prove neuroplasticity changes with stroke rehabilitation.

One of the ways such changes can be identified is through a neurophysiological study, which is captured as neurobiological signals. These specific signals can be sensed several ways, but established studies were based on functional magnetic resonance imaging, transcranial magnetic stimulation, and positron emission tomography scan [13-15]. In the majority of lower-income countries, these neuroimaging facilities are only limited to a few tertiary hospitals; thus, it is inconvenient to adopt such practice assessments in a contextual setting. Therefore, other methods of assessments must be sought, and the use of cheaper and conveniently accessible neurobiological signals need to be further investigated for this specific purpose.

Capturing neurobiological signals using electroencephalogram (EEG) that is cheaper and readily available would be more contextually plausible for identifying neuroplasticity changes with stroke rehabilitation. Various studies have been conducted for detecting neuroplasticity effect based on EEG signal analysis in stroke rehabilitation, but these studies are confined in investigating the direct effect of rehabilitation therapy on the neuroplasticity [16-20]. Further investigation on the relationship between neuroplasticity and rehabilitation therapy intensity after stroke were not evaluated in detail. Analyzing parameters of these neurobiological signals after rehabilitation therapy would provide in-depth knowledge on the relationship between neuroplasticity after stroke and therapy intensity.

The activation of neurobiological signals from the affected stroke areas should demonstrate incremental changes with time if rehabilitation therapy is conducted more frequently. It is hypothesized that the neuroplasticity changes occurring with rehabilitation can be objectively measured through the association between analyzed incremental changes derived from the EEG signals and the improved functional outcome measure scores. Based on this hypothesis, the dissimilarity in the associations observed with different rehabilitation frequency may demonstrate a dose-response relationship. The purpose of this study is to identify and determine the changes in the neurobiological signals from the EEG, to correlate these with the improved functional outcome measure scores after rehabilitation as an objective measurement of neuroplasticity, and to compare the associations observed in different therapy frequency for gait rehabilitation among subacute stroke individuals. These objectives are aimed through an interventional, randomized, single-blinded, controlled study.

## Methods

### Study Type, Blinding, Design, Randomization, Recruitment, and Intervention

The study will be an interventional, randomized, single-blinded, controlled study conducted at an outpatient rehabilitation setting among adult individuals with moderate to severe stroke in the subacute phase. Participants for the study will be recruited at a rehabilitation medicine clinic of a major tertiary hospital in the capital city of Sabah from the period of November 1, 2021, to October 31, 2022. Recruited participants and the in-charge physiotherapist will know the frequency of stroke rehabilitation intervention that each participant would be receiving. However, a separate neurophysiological technologist, EEG signals analyst, and therapist are to be assigned for measuring the outcome measures and analyzing the data without prior knowledge on the type of intervention that each participant will be subjected to.

Informed and recruited participants will be randomized into two groups: one group to receive a high frequency gait training (called the intervention group [IG]) and another group to receive the standard routine, low frequency gait training (called the control group [CG]), in a ratio of 1:1. The expected number of participants for each group is 18 (refer to the Sample Size section). The randomization plan for assigning treatment to each participant will be generated through online randomization software.

Each participant in the IG will have a therapy session three times a week, while a participant in the CG will have a therapy session once a week. Both groups will have to attend the session for a total of 12 consecutive weeks. Each session will last for approximately 40 minutes with a rate of perceived exertion between 3 to 5 minutes as the intensity threshold. The following training will be included: strengthening of hip flexors and knee extensors for approximately 5 minutes (Figure 1); balance training using a functional reach activity for approximately 10 minutes (Figure 2); gait training for approximately 20 minutes and to be conducted with or without walking aids and ankle-foot orthosis, depending on the stability, balance, and confidence level of the participants (Figure 3); and cooling down for approximately 5 minutes.

**Figure 1 figure1:**
[figure not shown]
Strengthening exercise for hip flexor and knee extensor.

**Figure 2 figure2:**
[figure not shown]
Functional reach for balance training.

**Figure 3 figure3:**
[figure not shown]
Flowchart on selecting mode of gait training.

### Variables and Outcome Measures

Two major independent variables for evaluation are patients’ demographic and stroke-related clinical information. Patient demographics shall include age, gender, and ethnicity. Stroke-related clinical information will incorporate the admission NIHSS score for classifying stroke severity, duration after stroke, and type of stroke.

The primary outcomes for assessment are brain wave frequencies and functional outcome measures. Brain wave frequencies from EEG signals will be conducted through resting-state EEG recordings at preintervention (R0) and postintervention (R1; within 2-4 weeks before the first and 2-4 weeks after the final therapy session) with the participant in a comfortable supine position. The participant will have to keep the eyes closed while awake and relaxed for 3 minutes during the EEG recording. The signals acquisition will require the use of a cap with 32 scalp monopolar electrodes placed according to the International 10/20 system.

Functional outcome measures based on the 6-Minute Walk Test (6MWT), Motor Assessment Scale (MAS), Berg Balance Scale (BBS), and Modified Barthel Index (MBI) will be assessed at preintervention (R0) and postintervention (R1; before the first and after the final therapy session). The 6MWT assesses endurance level through distance covered as a functional walking test [21]. The MAS is a performance-based scale for assessing everyday motor function in patients with stroke [22]. The BBS measures balance impairment, and its usability in poststroke assessment has been validated [23]. The MBI evaluates functional performances (feeding, bathing, grooming, dressing, bowel control, bladder control, toileting, chair transfer, ambulation, and stair climbing) with a maximum score of 100 [24].

### Statistical Analysis and Modeling

Descriptive analysis will be tabulated for demographics, clinical information, and functional measures. Descriptive data will be expressed as means and SDs unless otherwise stated. SPSS version 22 (IBM Corp) will be used for data analysis. One-way analysis of variance (ANOVA) will be used for analysis of normally distributed variables. Kruskal-Wallis ANOVA will be used for nonnormally distributed data. Categorical data will be analyzed using chi-square or Fisher exact test. A value of *P*<.05 is considered statistically significant. The data on the EEG signals will be displayed with graphs whenever appropriate.

The critical analytic comparisons will be as follows:

Changes of functional outcome measures based on the 6MWT, MAS, BBS, and MBI scores at R0 and R1 in the CG and IG groupsChanges of brain wave frequencies derived from EEG signals at R0 and R1 in the CG and IG groupsAdmission NIHSS score and admission lower extremity motor score based on NIHSS in the CG and IG groups

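### The plan names only one-way ANOVA or Kruskal-Wallis for outcomes measured before and after treatment; ANCOVA of R1 on arm with R0 as covariate would use the baseline and settle what is tested.

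*Protocol article*

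**What the plan says.** In the Protocol article, Statistical Analysis and Modeling names the tests by type of variable. "One-way analysis of variance (ANOVA) will be used for analysis of normally distributed variables", and "Kruskal-Wallis ANOVA will be used for nonnormally distributed data". Chi-square or Fisher exact tests cover categorical data, and "A value of *P*<.05 is considered statistically significant".

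The same section then lists the critical comparisons. The first is "Changes of functional outcome measures based on the 6MWT, MAS, BBS, and MBI scores at R0 and R1 in the CG and IG", the second is the matching comparison for the EEG brain waves, and the third is the admission NIHSS score and "admission lower extremity motor score based on NIHSS in the CG and IG groups".

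Variables and Outcome Measures confirms that the functional measures come from the same people twice: they "will be assessed at preintervention (R0) and postintervention (R1; before the first and after the final therapy session". EEG is also recorded at R0 and R1. Participants are randomised to two arms "in a ratio of 1:1". Association Analysis adds correlations between changes in the EEG ratios and changes in function, which are not a between-arm test of an outcome.

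**The concern.** One-way ANOVA has a single factor and assumes independent observations. The listed comparisons involve two arms and two time points, with two correlated values per person. The article does not say whether the test is applied to change scores, to R1 alone, or to R0 and R1 values as separate groups, and these choices do not behave alike. None of them uses R0 as a covariate, although it is collected on everyone.

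The trial is small: 18 per arm in one Methods section and 30 per arm in another (a discrepancy to be settled separately). At that size, chance baseline differences are common and precision is scarce. Comparing admission NIHSS between randomised arms as a critical analysis adds little, because under proper randomisation any difference there is due to chance.

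**Working it through.** **Inputs.** From the document: two arms, 1:1; n = 18 or 30 per arm; each outcome at R0 and R1; threshold 0.05 (two-sided assumed). Not in the document, so assumed: the R0–R1 correlation r, the SDs and the effect size. The article gives no power calculation, so there is no figure of its own to reproduce.

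**1. Between-arm variance under equal SDs.** In units of 2·SD²/n, the variance of the estimated arm difference is:
- R1 alone: 1
- change score: 2(1 − r)
- ANCOVA: 1 − r²

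The ratio of ANCOVA to change score is (1 − r²) / [2(1 − r)] = (1 + r)/2.

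| r (assumed) | change | ANCOVA | ratio | equivalent sample size |
|---|---|---|---|---|
| 0.3 | 1.40 | 0.91 | 0.65 | ×1.54 |
| 0.5 | 1.00 | 0.75 | 0.75 | ×1.33 |
| 0.7 | 0.60 | 0.51 | 0.85 | ×1.18 |
| 0.8 | 0.40 | 0.36 | 0.90 | ×1.11 |

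The difference detectable with 80% power is 2.80·√(2f/n), with f the factor above. At r = 0.7 it is 0.72 SD (change) against 0.67 SD (ANCOVA) for n = 18, and 0.56 against 0.52 SD for n = 30.

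**2. Unequal SDs.** Let k = SD(R1)/SD(R0), and work in units of the R0 variance. The change-score factor is 1 + k² − 2rk and the ANCOVA factor is k²(1 − r²). The first minus the second is (1 − rk)². This is never negative, but it is zero when rk = 1. Example with r = 0.8 and k = 1.25: change 1 + 1.5625 − 2.00 = 0.5625; ANCOVA 1.5625 × 0.36 = 0.5625. There is no gain.

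**3. Cost of estimating the covariates.** With q covariates that add nothing and N participants in total, variance rises by about q/(N − 3 − q). At N = 36 this is 1/32 = 3% for one covariate and 2/31 = 6% for two. At N = 60 it is 1/56 = 2% and 2/55 = 4%. With equal SDs, r = 0.8 and n = 18, the ratio 0.90 becomes 0.90 × 1.031 = 0.93 with R0 alone.

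**4. Chance baseline imbalance.** The baseline difference has SE √(2/n): 0.33 SD at n = 18 and 0.26 SD at n = 30. A gap above 0.3 SD arises in about 37% and 25% of trials respectively.

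**5. Behaviour of each reading.** Simulation with 2,000 runs per setting, equal SDs, r = 0.5, 0.7 and 0.8:
- *Change scores by arm.* With no treatment effect, rejection was 4.4% to 5.7%, so the test is valid. At r = 0.7 with a 0.6 SD effect, power was 0.63 against 0.69 for ANCOVA (n = 18), and 0.84 against 0.88 (n = 30).
- *R0 and R1 by arm as four separate groups.* With both arms improving by the same 0.6 SD and no treatment effect, it rejected in 50% to 54% of runs (n = 18) and 86% to 91% (n = 30). It responds to the shared improvement, not to the arm difference.
- *R0 against R1 within one arm, unpaired.* The SE is too large by 1/√(1 − r), which is 1.20 at r = 0.3 and 2.24 at r = 0.8. With no change at all, it rejected in 0 to 0.6% of runs instead of 5%.

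**The case against.** A reader might infer that the plan ignores pairing and so misstates its standard errors. The text does not support that as the main reading. The listed comparisons are of changes, and Association Analysis correlates one change with another, which requires a per-person difference. Differencing uses the pairing, and one-way ANOVA on differences in two arms is simply a t-test, unbiased under randomisation. The 1.2 to 2.2 times overstatement of the SE applies only to within-arm tests on raw values, so it is no argument for ANCOVA. This objection stands.

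It also stands that the gain rests on assumptions. The 11% end of the range is not a floor, because it needs equal SDs, and the 54% end needs r as low as 0.3. Adjustment is not quite free in a trial of 36, and adding NIHSS may not repay its degree of freedom, since eligibility confines it to 16–24. The article lists NIHSS as a comparison without tying a P value to it expressly.

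It can further be said that covariates are often left to a fuller document. That stands only in part: the article itself names the tests, and it leaves open which quantity they are applied to.

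**Conclusion.** The point holds as a moderate improvement, not as an invalid analysis. On the change-score reading, the stated test is sound but forgoes baseline adjustment. With equal SDs and r between 0.3 and 0.8, ANCOVA variance is 65% to 90% of the change-score variance, before about 3% (R0 only) to 6% (R0 and NIHSS) is given back at 18 per arm. If the SDs differ, the gain can be smaller or vanish. On the raw-value reading the test would be wrong for this design, but the article does not say that it will be used that way; it only fails to exclude it. Baseline-adjusted ANCOVA serves under every reading. It does not address the article's main hypothesis about correlations in the two arms, which is a separate matter.

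**What to change.** In Statistical Analysis and Modeling, replace the ANOVA and Kruskal-Wallis sentences, for the outcome comparisons, with:
- For each of 6MWT, MAS, BBS, MBI, DAR and DTABR, fit ANCOVA of the R1 value on arm with that outcome's R0 value as covariate. Report the adjusted IG minus CG difference with its 95% CI.
- Where residuals are clearly non-normal, use a rank-based ANCOVA in place of Kruskal-Wallis.
- Remove admission NIHSS and its lower-extremity score from the critical comparisons and tabulate them by arm. Admission NIHSS may be added as a second covariate if this is stated in advance, with little gain expected.

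If change scores are kept, the article should at least say that the test is on R1 minus R0 per person, compared between arms.

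The cost is wording and one or two degrees of freedom. R0 and NIHSS are already collected, and the SPSS package named in the article fits ANCOVA. By the Results section, analysis follows completion of all interventions, so on the article's own timeline the change can be made beforehand.

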### Quantitative EEG Indices Analysis

The brain wave frequencies derived from EEG signals are primarily captured for quantitative EEG (qEEG) indices analysis. The four main types of brain wave frequencies are delta (1-4 Hz), theta (4.1-8 Hz), alpha (8.1-12.5 Hz), and beta (12.6-30 Hz). In many established neurophysiological studies, two commonly used qEEG indices are delta to alpha ratio (DAR) and delta-plus-theta to alpha-plus-beta ratio (DTABR). DAR is proven to have the potential for improving the assessment of cerebrovascular pathology and found to be associated with NIHSS score after 30 days of stroke for prognostication [25]. On the other hand, NIHSS scores were not substantially linked with qEEG assessments of theta or beta waves. DTABR is considered as one of the best qEEG indices and demonstrated to be more superior than the ASPECTS measure for predicting poststroke outcome at discharge and up to 12 months after the event [26].

Data analysis for EEG signals will be performed offline in MATLAB (MathWorks) using the EEGLAB toolbox. This process will start by exporting the EEG raw data and saving it in the form of a Mat file for further evaluation. The EEG data is planned to be resampled at 500 Hz, then undergo several filters (bandpass, lowpass, and highpass) before being divided into consecutive nonoverlapping epochs, and will be mean detrended. The bad channels and segments containing gross artifacts that can be identified by visual inspection will be excluded. Next, independence component analysis will be used to eliminate other artifacts such as loss of electrode connections, ocular artifacts, and muscle artifacts. To extract the spectral power from the EEG data, each resultant component will undergo the time series, the topographic distribution of signal amplitudes, frequency spectra, and frequency loading. The spectral analysis will be done using a specific epoch of discrete fast Fourier transform to obtain and monitor certain frequency resolution.

### Ethics Consideration

This study has received the ethics approval from the National Medical Research Register of Malaysia, which is the formal and statutory body that governed all medical-related studies in this country, with ID no NMRR-19-3840-51591 (IIR).

## Results

Data analysis will be conducted after interventions are completed for all recruited patients. Of 24 eligible stroke patients attending the study site, we have recruited 18 participants so far and expect to publish our results in early 2023. The remaining 6 patients had logistic issues; hence, they were not able to participate in the study procedure.

## Discussion

The findings from this study would objectively demonstrate the enhanced neuroplasticity changes occurring with a higher frequency of rehabilitation training. The significance of these findings explain two major concepts in neuroplasticity post stroke: (1) the enhanced neuroplasticity implies that the stroke recovery with rehabilitation is exponential, likely due to a larger recruitment of synaptogenesis, and (2) a dose-response relationship for poststroke recovery. The dose refers to the frequency of therapy session, and the response reflects the neuroplasticity changes. Demonstrating this effect for the first time would permit a better understanding on the extent of stroke recovery so that the rehabilitation regime delivered is guided based on a more objective manner, rather than a blanket approach for all.

